Further evidence of the role that functional brain networks may play in modulating response to tDCS is available from other clinical populations. For example, in people with fibromyalgia, connectivity among the thalamus, posterior insula, motor cortex and sensory cortex was a marker of better analgesic response following tDCS applied to M1 [22]. Similarly, responses to tDCS applied to the dorsolateral prefrontal cortex in people in a minimally conscious state were associated with connectivity between the dorsolateral prefrontal cortex and inferior frontal gyrus [23]. It may be that the connectivity of the network targeted by tDCS can be a useful predictor of responsiveness to brain stimulation therapy. Indeed, this may be even more critical following a stroke, where damage as a result of the lesion can interrupt functional connectivity [24].

The primary objective of this study is to determine whether connectivity of the cortical target for tDCS modulates responses to this intervention in people with stroke. The secondary objectives of this study are to determine whether facilitatory tDCS applied to the ipsilesional hemisphere in combination with an upper limb exercise program provides greater behavioral improvement compared with sham stimulation and to determine whether additional neurophysiological characteristics, such as lesion size, cortical excitability, and white matter integrity, modulate the responsiveness to tDCS. We hypothesize that the response to anodal tDCS will be variable; participants who have greater functional connectivity of the ipsilesional motor network will have stronger responses to the stimulation as shown by a greater increase in upper limb function following the intervention period. Outcomes from this study will have important implications for the clinical translation of tDCS in stroke rehabilitation. The ability to select people who will respond to this therapy could substantially improve the clinical translation of this treatment approach.

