## Methods

### Study Design

The SPIRIT (Standard Protocol Items: Recommendations for interventional trials) recommendations were referenced when developing this protocol. This protocol has been registered in the Australian and New Zealand Clinical Trials Registry (ACTRN12618000443291). This study is a double blind, randomized controlled trial, with 2 parallel groups. Both outcome assessors and participants will be blind to allocation. Randomization will be performed using a computerized sequence generation by an external researcher. As our primary research aim is to investigate the brain connectivity of participants allocated to the active treatment group, the allocation will be weighted 2:1 toward the active treatment group. A sham treatment group will be used as a comparator to demonstrate the effectiveness of this intervention at the group level and to demonstrate that brain connectivity is not associated with response to sham tDCS.

The study protocol has been approved by the University of South Australia Human Research Ethics Committee (application identification 0000036781; approved May 19, 2017). Recruited participants will provide written informed consent in accordance with the World Medical Association Declaration of Helsinki.

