Inclusion criteriaAged ≥18 years of ageAt least 6 months after the first ever stroke with motor impairmentMeasurable impairment of the upper limb (Fugl-Meyer upper extremity of <62 out of 66)Supportive family, friends, or carers willing to actively assist and motivate across the 2-week interventionActive wrist extension of, at least, 5°Active index finger flexion of, at least, 10°Modified Ashworth scores of <4 for the affected elbow, wrist, and metacarpal phalangeal joints

Exclusion criteriaTranscranial magnetic stimulation and transcranial direct current stimulation safety exclusion criteria as per international guidelines [25]Contraindications for magnetic resonance imagingSelf-reported neglect, apraxia, or shoulder pain (>4 out of 10 on pain visual analog scale) that would affect the ability to undertake a 1-hour upper limb exercise program.Language or cognitive impairment that would limit the ability to communicate with the research team by videoconferenceParticipation in a concurrent research study or clinical program for upper limb rehabilitation.

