#### Assessments of Upper Limb Function

The primary outcome measure for this study is a change in upper limb impairment as measured with the Fugl-Meyer upper extremity (FM-UE) assessment. The FM-UE is a commonly used, validated, and reliable measure of sensorimotor impairment [30]. The FM-UE is considered as one of the most comprehensive quantitative measures of motor impairment following stroke.

In addition, upper limb function will be assessed with the action research arm test (ARAT) and grip strength. The ARAT is a valid and reliable measure of hemiplegic upper limb function [31]; it provides a quantitative measure of upper limb function for domains of grip, grasp, pinch, and gross arm movement. Grip strength is associated with motor cortical output and motor recovery [32]. We will measure grip strength using a hand dynamometer (SH5001 Saehan Hydraulic Hand Dynamometer, Saehan Co, Masan, Korea). The best (maximal) grip of 3 attempts will be recorded.

Strategies to facilitate protocol compliance.*Support person*: A support person will attend training for home transcranial direct current stimulation (tDCS) and graded repetitive arm supplementary program (GRASP) exercises to assist, and motivate, participants as required across the intervention.*Initial treatment under supervision*: The first treatment will be completed under supervision to ensure the correct use of tDCS.*TDCS electrode position marked on scalp*: The correct positioning of tDCS electrodes will be marked on the scalp with a permanent marker to facilitate home application.*Information sheet*: Step-by-step instructions for the use of the home stimulator.*Videoconference*: In real time, confirm correct tDCS usage, provide motivation, and progress individual exercise programs or GRASP grade. Videoconferences will occur every second day at a minimum and more frequently if required.*Exercise diary*: Record daily completion of tDCS and GRASP. Includes recording duration of GRASP therapy, motivation, fatigue, and perceived exercise difficulty.

Dependent variablesPrimaryChange in upper limb impairment (Fugl-Meyer Upper Extremity)SecondaryChange in the upper limb function (action research arm test)Change in the upper limb strength (grip strength)Change in the corticospinal excitability obtained from motor-evoked potential amplitude

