### Statistical Analysis

Normality of data will be confirmed using Shapiro-Wilk normality tests. Where required, data will be normalized using transformations or nonparametric statistics applied. Participants’ demographics and clinical characteristics will be compared between active and sham groups. The effect of the intervention on behavioral and neurophysiological outcome measures will be investigated with a 2 Group (active, sham) × 4 Time Point (Baseline, Postintervention, 1-Month Follow-up, 3-Month Follow-up) repeated measures analysis of variance. Independent variables (Textbox 5) will be correlated with the primary outcome measure for response to anodal tDCS (change in upper limb impairment measured with the UE-FM). Where appropriate, regression models will be generated using those independent variables significantly correlated with change in upper limb impairment to identify a combination of measures associated with response to anodal tDCS. Any regression models generated will be compared using the Bayesian information criteria [45]. Where appropriate, the predictive capacity of the generated model will be investigated using a leave-one-out cross-validation. This cross-validation will be performed on participants allocated to both active and sham treatment groups to demonstrate that the predictive model is specific to the stimulation group. Statistical testing will be performed using SPSS (IBM Co, version 24.0) and significance level will be *P* ≤.05.

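### The active-versus-sham ANOVA treats baseline as a fourth outcome level; conditioning on baseline and naming one leading contrast would use the data better and give an effect estimate

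*Protocol article*

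**What the plan says.** The Statistical Analysis section of the protocol article states: "The effect of the intervention on behavioral and neurophysiological outcome measures will be investigated with a 2 Group (active, sham"), crossed with "4 Time Point (Baseline, Postintervention, 1-Month Follow-up, 3-Month Follow-up) repeated measures analysis of variance". Baseline is therefore one of the four levels of the repeated outcome. No baseline covariate is named. The only other use of baseline data in the group comparison is descriptive: "Participants’ demographics and clinical characteristics will be compared between active and sham groups".

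This analysis serves a secondary objective in the Introduction, namely "whether facilitatory tDCS applied to the ipsilesional hemisphere in combination with an upper limb exercise program provides greater behavioral improvement compared with sham stimulation". Study Design gives the sham arm the same purpose: "A sham treatment group will be used as a comparator to demonstrate the effectiveness of this intervention at the group level". The outcome most affected is the primary one: "The primary outcome measure for this study is a change in upper limb impairment as measured with the Fugl-Meyer upper extremity (FM-UE) assessment". The Sample Size section gives 45 active and 23 sham participants and allows 30% dropout. Its power calculation is for a correlation, and no power is stated for active versus sham.

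**The concern.** A pre-treatment score cannot respond to treatment. With baseline as a fourth outcome level, the evidence of benefit sits in a Group × Time interaction with 3 degrees of freedom. This has two consequences.

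- The interaction uses baseline only by subtraction. It does not condition on it, so an arm that starts lower by chance still gains a little from regression to the mean, and residual variance is higher than it need be.
- A significant 3-df interaction says that the arms' profiles differ. It does not say by how much, at which visit or in which direction.

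At stake is how much a trial with 23 sham participants can say about benefit over sham, and whether it reports that benefit as an estimate with an interval.

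**Working it through.** **Inputs.** From the documents: 45 and 23 participants; 30% dropout, which leaves 45 × 0.7 = 31.5 and 23 × 0.7 = 16.1, taken as 31 and 16; alpha .05; one baseline and three later visits. Assumed: equal variances and equal correlation ρ between any two visits. The documents give no ρ, so a range is shown. There is no stated power for this comparison to reproduce. The article does not say which ANOVA term carries the test. I take Group × Time, the favourable reading, since a group main effect would be diluted by the baseline visit.

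**Step 1: what the covariate adds.** Take the outcome as the mean of the three later visits, with unit variance per visit.

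- Change-score variance: (1+2ρ)/3 + 1 − 2ρ = 4(1−ρ)/3.
- Baseline-adjusted variance: (1+2ρ)/3 − ρ².
- Example at ρ = 0.7: (0.80 − 0.49)/0.40 = 0.775.

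Set the effect so that the adjusted test has Z = 2.80, which gives Φ(2.80 − 1.96) = 80%. The change score then has Φ(2.80√ratio − 1.96).

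| ρ | variance ratio | change-score power | gain from covariate |
|---|---|---|---|
| 0.7 | 0.775 | 69% | 11 points |
| 0.8 | 0.850 | 73% | 7 points |
| 0.9 | 0.925 | 77% | 3 points |
| 0.95 | 0.9625 | 78% | 2 points |

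These are large-sample values. Allowing for the estimated covariate, simulation puts the gain at about 10 points at ρ = 0.7 and 1-2 points at 0.9 or above (separate runs ranged from 0 to 3 there).

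**Step 2: what the 1-df contrast adds.** With a constant effect δ at the three later visits, the between-arm differences are (0, δ, δ, δ) and their mean is 0.75δ. The sum of squared deviations is 0.5625δ² + 3 × 0.0625δ² = 0.75δ². The interaction's noncentrality is (n₁n₀/n) × 0.75δ²/(1−ρ). The change score has exactly the same value, since 1/[4(1−ρ)/3] = 0.75/(1−ρ). The two tests therefore hold the same information, and the interaction spreads it over 3 df. Simulated power at 45:23 (6,000 trials per row, adjusted test set near 79%):

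| ρ | planned interaction | change score | baseline-adjusted average |
|---|---|---|---|
| 0.5 | 43% | 60% | 79% |
| 0.7 | 52% | 69% | 79% |
| 0.8 | 56% | 71% | 78% |
| 0.9 | 59% | 76% | 79% |
| 0.95 | 62% | 76% | 78% |

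A separate run gave 52-61% against 76-79% for ρ from 0.7 to 0.95. Results at 31:16 are nearly the same when the effect is rescaled. All tests hold about 5% under the null.

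**Step 3: what happens if the effect fades.** Keep the mean effect but let it run 1.5 : 1 : 0.5. The differences (0, 1.5δ, δ, 0.5δ) still average 0.75δ. The sum of squared deviations is now 0.5625 + 0.5625 + 0.0625 + 0.0625 = 1.25 (in δ²). The interaction's noncentrality rises by 1.25/0.75 = 1.67, while the average contrast gains nothing. Simulated power, interaction against adjusted average: 77% against 79% at ρ = 0.7, and 84% against 78% at ρ = 0.9.

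**Step 4: the choice of contrast.** With a fade of 1 : 0.6 : 0.3, the adjusted postintervention visit alone has 91-92% power, against 75% (ρ = 0.7) and 84% (ρ = 0.9) for the interaction. With a constant effect that single visit has no clear advantage: 84% against 83% at ρ = 0.7, and 80% against 83% at ρ = 0.9 (effect set so that a single-visit change analysis has about 80%).

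**Step 5: chance baseline imbalance.** The standard error of the raw baseline difference is √(1/45 + 1/23) = 0.256 SD. Only (1−ρ) of a baseline difference reaches a change-score estimate: 0.3 × 0.256 = 0.08 SD at ρ = 0.7, 0.03 SD at 0.9 and 0.01 SD at 0.95.

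**The case against.** The planned test is valid, and under randomization its change contrasts are unbiased on average. A condensed article may leave covariates and named contrasts to a fuller document. The comparison is secondary; the sample size and 2:1 allocation serve the connectivity question. Treatment lasts two weeks and the last visit comes three months later, so a fading effect is plausible, and Step 3 shows that an averaged contrast can then lose to the planned interaction.

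Most of this stands, and it rules out three stronger readings that a reader might infer.

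- **That the change is free of any downside.** It needs no new data, but the averaged contrast can lose power when the effect merely fades, without any change of sign. That loss comes from averaging, not from conditioning on baseline. In the 1 : 0.6 : 0.3 case, a large-sample calculation gives a baseline-adjusted 3-df test 83% against 76% for the planned one at ρ = 0.7, and 85% against 84% at ρ = 0.9.
- **That a chance imbalance of about 0.26 SD contaminates the result.** The interaction already subtracts baseline, so Step 5 applies. Entry by "Fugl-Meyer upper extremity of <62 out of 66" also comes with wrist, finger and spasticity criteria, so it is less open than it looks alone.
- **That leaving baseline unadjusted explains the whole power gap.** At high ρ nearly all of it comes from the degrees of freedom.

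The point about condensation stands only in part. The article states the method and places baseline inside the time factor, so that choice can be assessed as written. Its silence on stratification is not held against it.

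**Conclusion.** The concern holds as a matter of efficiency and reporting. Treating baseline as an outcome level leaves precision unused and ends in an omnibus test without an effect estimate. The covariate itself is worth about 10 power points at ρ = 0.7 and 1-2 points at 0.9 or above. The rise from about 52-61% to 76-79% depends mainly on the 1-df contrast and holds only for a roughly constant effect. With a 1.5 : 1 : 0.5 fade at ρ = 0.9 it reverses, to 78% against 84%.

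All sizes rest on an undocumented ρ, equal correlation between visits, normal scores and complete data. The documents do not support calling the planned analysis invalid or biased. The change is worth making, but nothing in the primary connectivity question depends on it.

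**What to change.** In the Statistical Analysis section, replace the 2 × 4 ANOVA for FM-UE, ARAT and grip strength. Model the three post-baseline visits with group, visit and their interaction, and with the baseline value of the same measure as covariate. Prespecify one leading contrast before unblinding, for example the postintervention visit or the average over follow-up, and give the reason in terms of the expected time course. Report the adjusted active-minus-sham difference with 95% CI at each visit, with the non-leading visits as supportive.

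The cost is a sentence or two of text and one degree of freedom for the covariate. Baseline values are already collected, so no new data are needed. The remaining risk is choosing a contrast that does not match the true time course, which is why it must be fixed in advance.

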**Methods:**

This study is a double blind, randomized controlled trial (RCT), with two parallel groups. A total of 68 participants with first ever ischemic stroke with motor impairment will undertake a two week (14 session) treatment for upper limb function (Graded Repetitive Arm Supplementary Program; GRASP). Participants will be randomized 2:1 to active:sham treatment groups. Those in the active treatment group will receive anodal transcranial direct current stimulation to the ipsilesional motor cortex at the start of each GRASP session. Those allocated to the sham treatment group will receive sham transcranial direct current stimulation. Behavioural assessments of upper limb function will be performed at baseline, post treatment, 1 month follow-up and 3 months follow-up. Neurophysiological assessments will include magnetic resonance imaging (MRI), electroencephalography (EEG) and transcranial magnetic stimulation (TMS) and will be performed at baseline, post treatment, 1 month follow-up (EEG and TMS only) and 3 months follow-up (EEG and TMS only).

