### Neurophysiological Testing

#### Electroencephalography

Functional connectivity between brain regions will be assessed with high-density EEG. Three minutes of EEG will be acquired using an ASA-lab EEG system (ANT Neuro, Enschede, the Netherlands). Participants will be fitted with an ANT Waveguard cap with 64 sintered Ag-AgCl monopolar electrodes in standard 10-10 positions. Signals will be sampled at 2048 Hz, amplified 20X, filtered (high pass, DC; low pass, 553 Hz) and online referenced to CPz. During data recording, participants will be seated in a comfortable chair in a quiet room. Standardized instructions will be delivered to each participant asking them to relax during the 3 minutes of data recording, keep their eyes open, refrain from speaking or moving, maintain their gaze toward a fixation point straight ahead at eye level and not actively engage in any cognitive or mental tasks. Impedance will be kept <5 kΩ while recording.

Artifact rejection will be performed prior to analysis using independent component analysis. Nonphysiological artifacts will be identified using an automated and objective method to remove assessor bias [35]. Preprocessed data of participants with a right hemisphere lesion will then be flipped about the midline so that all lesions appear in the left hemisphere. Functional connectivity between electrodes will be determined using the debiased weighted phase lag index, which is a conservative estimate of connectivity based on phase consistency and biasing against zero phase lag relationships, limiting the detection of spurious measures of connectivity [36]. Regions of interest will include a seed approximating the ipsilesional M1 (C3) and clusters of electrodes approximating the ipsilesional premotor (F5, F3, FC5, and FC3), ipsilesional parietal (CP3, CP5, P3, and P5), and contralesional M1 (C4). Frequency bands of interest are the alpha band (8-15 Hz) and beta band (16-31 Hz) as they are associated with sensorimotor function [20,37,38]. For a given frequency, a debiased weighted phase lag index value of 1 indicates maximal phase coupling, whereas a value of 0 indicates no phase coupling. Connectivity analyses will be performed in MATLAB 9.2.0 (MathWorks, Inc) using both EEGLAB [39] and FieldTrip toolboxes [40].

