For resting state fMRI, nuisance regressors of no-interest (cerebrospinal fluid, white matter, head motion, and physiological noise) will be modeled and removed. We will then calculate the mean time course of the blood-oxygenation level dependent signal in all voxels of the ipsilesional M1 region of interest. This time series will then be entered separately as an explanatory variable in the general linear model to determine for each participant the voxels where blood-oxygenation level dependent signal is temporally correlated with the ipsilesional M1. Connectivity between the ipsilesional M1 and other regions of interest (contralesional M1, ipsilesional dorsal premotor cortex, ipsilesional ventral premotor cortex, ipsilesional supplementary motor area, and ipsilesional posterior parietal cortex) will be determined with a Pearson’s correlation coefficient. Connectivity of the ipsilesional M1 will be compared before and after tDCS with a general linear model.

Structural connectivity will be analyzed with the FMRIB Diffusion Toolbox [44]. For each participant, the mean fractional anisotropy (FA) of the posterior limb of the internal capsule will be determined. An asymmetry index will be calculated as follows: FA = (FA–FA) / (FA+FA).

Lesion volume will be defined by manually tracing the lesion in FLS view. Lesions will be traced from each participant’s T1-weighted image using the coregistered T2-weighted image as a reference for lesion extension.

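### At least 18 predictors are screened at an unadjusted P≤.05 with no primary predictor or visit named, although the trial is sized for one correlation at alpha .05

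*Protocol article*

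**What the plan says.** **The screen.** In Statistical Analysis, "Independent variables (Textbox 5) will be correlated with the primary outcome measure for response to anodal tDCS". Then, with the qualifier that this happens where appropriate, "regression models will be generated using those independent variables significantly correlated with change in upper limb impairment". One level applies throughout: "significance level will be *P* ≤.05". Models are compared by the Bayesian information criterion (BIC). Where appropriate they are checked by leave-one-out cross-validation in the active and sham groups.

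**The predictors.** Textbox 5 lists functional connectivity (task fMRI, resting-state fMRI, EEG), a fractional anisotropy (FA) index, lesion volume and four demographic or clinical variables. The measurement sections expand this list:
- EEG: "Regions of interest will include a seed approximating the ipsilesional M1 (C3) and clusters of electrodes approximating the ipsilesional premotor", together with a parietal cluster and contralesional M1, in an alpha (8-15 Hz) and a beta (16-31 Hz) band.
- Resting-state fMRI: ipsilesional M1 paired with "other regions of interest (contralesional M1, ipsilesional dorsal premotor cortex, ipsilesional ventral premotor cortex, ipsilesional supplementary motor area, and ipsilesional posterior parietal cortex".

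**The outcome.** Assessments of Upper Limb Function defines the primary outcome as a change in FM-UE and gives no visit. The Abstract says "Behavioural assessments of upper limb function will be performed at baseline, post treatment, 1 month follow-up and 3 months follow-up". The hypothesis in the Introduction refers only to the time after the intervention period.

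**The design basis.** Sample Size uses a single pilot correlation, r=0.56, between high beta connectivity and change in cortical excitability, with alpha .05 and 95% power, giving 47 before inflation to 68.

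**A secondary objective.** The Introduction asks whether "additional neurophysiological characteristics, such as lesion size, cortical excitability, and white matter integrity, modulate the responsiveness to tDCS".

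**The concern.** The primary claim would be that connectivity of the stimulated network predicts response to tDCS. Under the stated rule, that claim can come from any one of many correlations, each tested at .05. The alpha of .05 used for the sample size therefore does not describe the error rate of the planned analysis.

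This is more than a detail left to an analysis plan. The article fixes the selection rule, which is significance at an unadjusted level, so a later adjustment would change a stated rule.

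The Discussion intends the biomarkers to guide who receives tDCS. A chance predictor would misdirect that selection.

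A smaller, separate point is that baseline cortical excitability is named as a modulator in the objectives but is absent from Textbox 5. Corticospinal excitability appears only as a change outcome in Textbox 4, so this part of the secondary objective has no listed analysis.

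**Working it through.** **The plan's own figure.** The two-sided Fisher formula is n = ((1.960 + 1.645)/atanh(0.56))² + 3. With atanh(0.56) = 0.633 it gives 35.4, so 36, and not 47. The same formula gives 47 if r is 0.50. The inflation does reproduce: 47 × 1.12 × 1.30 = 68.4, so 68. The mismatch at 47 is a separate matter, and nothing below depends on it. What matters here is that the calculation is for one test at .05.

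**Counting the predictors.**

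| Source | Count |
|---|---|
| EEG: C3 to 3 regions × 2 bands | 6 |
| Resting-state fMRI: M1 to 5 regions | 5 |
| Task fMRI (the analysis is of activation maps, so a minimum) | 1 |
| FA asymmetry index | 1 |
| Lesion volume | 1 |
| Age, gender, time since stroke, affected hemisphere | 4 |
| **Total** | **18** |

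The functional connectivity measures alone number 6 + 5 = 11, or 12 with task fMRI.

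**Chance of at least one P≤.05 at one visit when nothing is related, independent tests: 1 − 0.95^k.**
- k = 11: 43%
- k = 12: 46%
- k = 18: 60%, with 18 × 0.05 = 0.9 false positives expected

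**Counting only the hypothesised direction** (greater connectivity, stronger response), at 0.025 in that tail: 1 − 0.975^11 = 24%, and 1 − 0.975^12 = 26%.

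**Correlated predictors.** The documents give no correlations among predictors, so the values below are assumptions. The figures come from simulation under the global null with two-sided tests. Sample sizes were n = 45 (the planned active arm) and n = 31 (45 × 0.70 = 31.5 after the allowed 30% dropout). The two sizes gave nearly the same results.

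| Common correlation | 11-12 connectivity measures | All 18 |
|---|---|---|
| 0 | 43-47% | 60-61% |
| 0.3 | 38-40% | 51-52% |
| 0.5 | 31-33% | 40-41% |
| 0.7 | 22-24% | 28-29% |

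If correlation exists only within a modality, the figures are higher. For all 18 variables they are about 55% at 0.5 and 49-50% at 0.7. For the 12 connectivity measures they are 38-39% and 32-33%.

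**If the visit were also chosen afterwards.** With changes at the three visits correlated 0.8, all 18 variables give 84-85% if independent, 64-65% at a common correlation of 0.5 and 48% at 0.7.

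**The case against.** **A chance biomarker is more likely than not.** A reader might infer this from the 60% figure. The documents do not support it as a general statement. The 60% needs 18 independent tests, and six of the 18 are age, gender, time since stroke, affected hemisphere, lesion volume and FA. A chance correlation with age is not a false finding about functional connectivity. The 11 or 12 connectivity measures stay below 50% at one visit even if independent, and all 18 also fall below 50% under a strong common correlation.

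**The error is 75-85%.** A reader might reach this by counting all three visits. No section plans a choice among visits. The text is silent on the visit, and a condensed article may leave that to a fuller document. The open visit is a looseness that can raise the error, not a stated analysis.

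**The hypothesis is directional.** This stands as a mitigation: it brings the figure for 11 independent measures down to 24%. But the plan does not state one-sided testing, and 24% is still nearly five times 5%.

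**The plan has safeguards.** It does list a BIC comparison, leave-one-out cross-validation and a check in the sham arm. BIC compares only models built from variables that passed the screen. The cross-validation is applied to a model already generated, after the screen has used every participant, so its predictions are not independent of the selection. A chance predictor in the active arm will usually fail among 23 sham participants, and that failure would be read as evidence that the model is specific to stimulation. These steps are sensible, but they do not control the error of the screen.

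**Multiplicity methods belong in an analysis plan.** This is fair in general. Here, however, the article itself states the unadjusted selection rule.

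**Conclusion.** The point holds in this form: the plan screens at least 18 variables at an unadjusted .05, names no primary predictor and no primary visit, and is sized for one correlation at .05. At one visit, the chance of at least one false positive among the 11-12 connectivity measures is 43-46% if they are independent and about 22-33% at common correlations of 0.7 to 0.5. For all 18 it is 60% and about 28-41%. It is higher if the visit is chosen afterwards.

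These figures assume that no predictor is related to FM-UE change, that tests are two-sided, and that correlations among predictors lie in the range shown. Even the lowest two-sided figure is more than four times the stated 5%. The count and the stated rule are certain. The exact error rate is not.

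The omission of baseline cortical excitability from Textbox 5 is a separate inconsistency and adds nothing to the error rate.

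**What to change.** Before data are examined:

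1. Name one confirmatory test at .05: one connectivity measure (modality, region pair and, for EEG, band) against FM-UE change at one visit, for example baseline to post-intervention. Which measure is the sponsor's choice. If it is an EEG measure, reconcile the bands first. The Introduction reports high beta (20-30 Hz) in healthy adults and alpha (8-13 Hz) in people with stroke. Sample Size cites high beta from the same stroke study, and the Electroencephalography section lists only 8-15 and 16-31 Hz.
2. Alternatively, apply Holm across the connectivity family at one named visit.
3. Label all other predictors, bands and visits exploratory, with Holm- or FDR-adjusted P values.
4. Repeat the predictor selection inside each leave-one-out fold.
5. Add baseline cortical excitability to the exploratory predictors.

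**Cost.** This is a change of analysis wording and needs no new data. The other predictors lose confirmatory status.

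The choice between items 1 and 2 affects power. Taking r = 0.56 at face value (it was observed for a different outcome) and the Fisher approximation, one test at .05 has about 98% power with 45 active participants and 92% with 31. At the strictest Holm step for 12 measures, 0.05/12 = 0.0042, power is about 89% and 69%. Bonferroni over all 18, at 0.05/18 = 0.0028, gives about 87% and 64%.
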